### Treatment

Randomized patients receive state-of-the-art burn care treatment including (depending on the clinical situation of the individual patient) analgosedation, respiration, escharectomy and split skin grafting or, if necessary, temporary wound closure. General wound care and wound dressings can be used, as they are standard practice in the study centers. The only exceptions are the studied split SGDS, the studied second-degree wound and the studied third-degree wound, which have to be treated as described in detail in the study protocol.

The study medication is either 150 IU recombinant human EPO (rhEPO) (NeoRecormon Multidose 50,000 IU, Roche, Grenzach-Wylen, Germany) per kilogram of body weight or a matched placebo (see Table 
2), which is administered every other day subcutaneously for 21 days. The split SGDS is to be generated on Day 2 of study treatment and special wound dressings with a polyurethane foil have to be applied according to the trial protocol. Dressing changes and wound controls are made at specified time points. Patients receive a standardized anticoagulant therapy with body weight-adjusted intravenous heparin.

**Table 2 T2:** Composition of placebo solution

**Substance**	**Amount**
NaCl	8.24 g
Benzyl alcohol	3.67 g
Benzalkonium chloride	0.58 g
H_2_O ad injectionem	Ad 1,000 ml

### Measurements

Race, gender, age, height, weight, TBS burned percentage, severity of burn (grades 1, 2a, 2b or 3), ABSI and concomitant illnesses or injuries will be documented upon admission. Woman of reproductive age will undergo a pregnancy test to check for an unknown pregnancy.

Daily controls of the organ failure parameters, using the sequential organ failure assessment (SOFA), and safety relevant parameters will be performed. The wound will be clinically assessed and photographs taken according to the protocol. Special EPO-related blood samples will be taken once a week for four consecutive weeks. Punch biopsies will be performed from the SGDS and the SDW four times and once from healthy skin as a control.

### Primary endpoint

The primary endpoint is the time until complete re-epithelialization of the SGDS at a specified location on the lateral upper thigh.

### Secondary endpoints

Time until complete wound healing of type 2a SDW

Time until complete wound healing of skin graft.

Cellular and molecular regenerative effects in SGDS and type 2a SDW, Endothelial.

Progenitor Cell (EPC) recruitment, EPO receptor up-or down-regulation, protein-, RNA- and microRNA- expression patterns

Quality of scar formation in conservatively and operatively treated wound locations.

Number of packed red cells units, which are transfused during the treatment interval- Organ dysfunction parameters- Quality of life 12 months after trauma (SF-36)- Mortality (within 21 days, during the hospital stay and 1 year on).

Adverse events (AEs), Serious Adverse Events (SAEs), Suspected Unexpected Serious.

Adverse Reactions (SUSARs)

Gender differences in monitored data.

### Safety data

The safety endpoints include AEs, SAEs, SUSARs, laboratory test results and vital signs. The data safety monitoring board (DSMB) will supervise the occurrence of AEs, SAEs, SUSARs and overall safety parameters.

A group of independent experts will form the Safety Monitoring Board. The DSMB will independently review the safety data for the duration of the study. In addition, the coordinating investigator will inform the DSMB of any SUSARs with a written report.

The DSMB will give advice when specific actions are necessary. The study sites will be immediately informed of the procedures. The DSMB will discontinue the study if a quantitative accumulation of SAEs is observed. In addition, if there is an unexpected accumulation of SAEs other than mentioned above during the study, the DSMB will discontinue the study. Additionally, annual safety and progress reports have to be prepared for the authorities and the independent ethics committees.

### Statistical considerations

#### Sample size justification

Under conventional treatment, complete re-epithelialization of split skin graft donor sites occurs after a mean of 10 to 15 days with a standard deviation (SD) of about 6 days, depending on the donor site and the patient’s general condition. We expect that EPO treatment can reduce the total healing time by at least 4 days. Sample size calculation with alpha = 0.05 and beta = 0.10 thus indicates that 48 evaluable patients per group are necessary. In order to have 96 patients with valid data for the intention-to-treat analysis of the primary outcome, we aim to include 150 patients. This allows for 54 dropouts (34%).

#### Statistical analysis

Analyses will include all randomized patients with at least one exposure to the study drug. In addition to the intention-to-treat population, an exploratory analysis of all patients completing the study as planned (per protocol analysis) will be carried out. Standard statistical testing will be used to examine the superiority of one treatment arm. Testing will be adjusted for two stratification factors: ABSI group and hospital. The primary endpoint for the time taken for re-epithelialization of the skin graft donor site will be analyzed as a continuous variable with normal distribution. A safety analysis will be carried out for all adverse events (regardless of severity). According to current standards, the safety analysis will exclude those patients who failed to receive any study drug dose. A list of all adverse events will be provided and periodically distributed to the DSMB. The two-sided significance level for the final analysis is 0.05.

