The fact that no increase in hemoglobin, hematocrit, reticulocyte or erythrocyte count was found in either study is an especially interesting aspect regarding the treatment of burned patients; besides the well-known fact of decreased EPO efficacy regarding erytropoiesis in inflammation and in trauma situations of the organism, no explanation for this phenomenon has been given so far.

Known complications of EPO treatment are thromboembolic events. A large multi-center trial investigating the safety of EPO administration to poly-traumatized patients demonstrated EPO is safe and beneficial for these patients and that thromboembolic events were reduced to ranges seen in poly-traumatized patients not receiving EPO when combined with an appropriate anti-thrombotic therapy
[38]. As the thromboembolic risk of thermally injured patients is comparable to that of poly-traumatized patients, we conclude that EPO administration in thermally injured patients is safe when combined with an adequate anti-thrombotic prophylaxis as it is done in our trial.

There are two further well-known adverse events related to EPO. The first is the increase in blood pressure in already hypertonic patients
[39] with the consequence that therapy resistant arterial hypertension is an exclusion criterion of the trial. The second is the unclear situation of EPO in patients with malignant tumors. In several trials it was shown that the mortality rate of EPO-treated groups is higher than for untreated controls
[39]. Therefore, a known malignancy is also an exclusion criterion of the trial.

Age, nutritional status, affected total body surface, gender, concomitant illnesses, inhalation injury or other concomitant trauma, as well as wound infections, have a large influence on the patient’s prognosis, survival rate and wound healing. Therefore we considered all of these factors carefully and discussed their relevance for our primary and secondary endpoints. As we are unable to foresee which patient group will profit most, we consider an exclusion of one of this groups as unethical.

Dermal thermal traumas are commonly seen in two age groups of adults. The first group comprises young adults aged between 18 and 28 and the second group comprises elderly persons aged over 65 years. As we are not able to foresee which of these groups would benefit most from pro-regenerative treatment, we decided to include patients aged 18 to 75 in our study
[40].

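### The primary analysis uses burn severity only as a grouped score; adding recorded age, burned area and sex as covariates would cost little and could modestly improve precision

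*Protocol article*

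**What the plan says.** Statistical analysis section: "Testing will be adjusted for two stratification factors: ABSI group and hospital". No other covariate is named. The primary endpoint, time to re-epithelialization of the donor site, is treated there as continuous and normally distributed, and "The two-sided significance level for the final analysis is 0.05".

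Discussion: "Age, nutritional status, affected total body surface, gender, concomitant illnesses, inhalation injury or other concomitant trauma" and wound infections are said to have a large influence on prognosis, survival and wound healing, and their relevance to the primary and secondary endpoints is said to have been considered. A later paragraph repeats the point for burned surface and burn degree in combination with age and gender. It also gives the centres' differing nutrition regimes as one reason for adjusting for hospital.

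Measurements: the admission record includes "Race, gender, age, height, weight, TBS burned percentage, severity of burn (grades 1, 2a, 2b or 3), ABSI".

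Sample size justification: "Sample size calculation with alpha = 0.05 and beta = 0.10", with treatment expected to "reduce the total healing time by at least 4 days", healing times "with a standard deviation (SD) of about 6 days", and 48 evaluable patients per group.

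The article does not define the ABSI groups or list the items of the index, which it describes only as a burn severity index. It does not say whether the SD of 6 days is before or after adjustment.

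**The concern.** The plan names certain patient characteristics as strong influences on healing, collects them before treatment, and then carries severity into the primary model only as a grouped score. Grouping discards differences between patients within a group. The population is wide: ages 18 to 75, and burns from 5% to 60% of body surface, with no upper limit below age 40. If age and burned area predict donor-site healing beyond the ABSI group, the residual variance is larger than it needs to be and the confidence interval for the treatment difference is wider. Because the outcome is analysed as continuous, baseline covariates can be added directly. They must be chosen before unblinding to be credible.

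**Working it through.** **1. Reproduce the plan's figure.** Inputs from the Sample size justification and Statistical analysis sections: difference 4 days, SD 6 days, two-sided alpha 0.05, power 0.90, equal groups.

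n per arm = 2 × [SD × (1.960 + 1.282) / 4]² = 2 × (6 × 3.242 / 4)² = 47.28, rounded up to 48.

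This matches the plan. A one-sided test would need 39, so the stated figure is two-sided. Power at 48 per arm is 90.4% by the normal approximation and 89.8% by the noncentral t.

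**2. Effect of added covariates.** Let R² be the share of the variance remaining after ABSI group and hospital that age, burned area and sex explain. The document gives no value, so 0 to 0.20 is assumed. The SD of 6 is also assumed to be the residual SD after ABSI group and hospital.

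Residual SD = 6 × √(1 − R²). CI half-width = 1.96 × SD × √(2/48).

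Degrees of freedom: 96 − 1 (intercept) − 1 (treatment) − 12 (13 hospitals) − 2 (three ABSI groups, assumed) = 80; three further covariates leave 77.

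| Extra R² | Residual SD (days) | n per arm for 90% | Power at 48 per arm, normal | Power, noncentral t, 77 df | 95% CI half-width (days) |
|---|---|---|---|---|---|
| 0 | 6.00 | 48 | 90.4% | 89.7% | 2.40 |
| 0.05 | 5.85 | 45 | 91.8% | 91.1% | 2.34 |
| 0.10 | 5.69 | 43 | 93.1% | 92.5% | 2.28 |
| 0.20 | 5.37 | 38 | 95.5% | 95.0% | 2.15 |

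At R² = 0, going from 80 to 77 degrees of freedom costs less than 0.1 percentage point.

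**3. Allow for what the ABSI group already carries.** Suppose, as an assumption the article neither states nor excludes, that the ABSI group is a banding of one normally distributed score holding the age and burned-area information. Equal-sized bands then keep a share c of it: 64% with 2 bands, 79% with 3, 86% with 4. If the full score explains R² of the variance, the extra share left after banding is R²(1 − c) / (1 − cR²).

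- 2 bands: R² 0.10 gives 0.10 × 0.363 / (1 − 0.064) = 0.039; R² 0.30 gives 0.30 × 0.363 / (1 − 0.191) = 0.135.
- 3 bands: 0.022 and 0.081.
- 4 bands: 0.015 and 0.056.

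Over about 0.015 to 0.14, power at 48 per arm is about 91% to 94% (normal approximation), or 90% to 93% by the noncentral t.

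**4. A cost the table omits.** Covariates unrelated to outcome still correlate with treatment by chance. With simple randomization, three of them cost on average about 3/80, or 4%, of the information. Stratifying by ABSI group reduces this for whatever the index captures. An extra R² of only a few percent would therefore bring no net gain.

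**The case against.** The strongest reply is that nothing here is wrong. Adjusting for the stratification factors is sound practice, and the planned size meets its 90% target without more covariates. That stands, so a reader who inferred that the primary analysis is invalid or the trial underpowered would have no support in the document.

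Second, burn severity is already in the model through ABSI group, which is also a stratification factor. It is tempting to say that chance imbalance in age or burned area is likely and goes uncorrected. The document does not support that: stratifying by and adjusting for ABSI group already deal with part of it. Only variation within groups, and anything the index does not capture, is unused.

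Third, the Discussion speaks of prognosis, survival and wound healing together, gives no figure, and is arguing against excluding patient groups rather than choosing covariates. The primary endpoint is a surgically created wound at a specified site on the thigh. A large influence on burn wounds need not mean a large influence there. This also stands, and is why the range must include zero.

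Fourth, the article condenses a fuller protocol and does not say that these two factors are the only ones. If the full analysis plan already lists further baseline covariates, the point is met. As published, though, the article states a definite adjustment set, and changing it is a specific proposal rather than a complaint about missing detail.

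These arguments reduce the size and urgency of the point without removing the case for considering it.

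**Conclusion.** The point holds as a low-cost improvement to a valid analysis. At 48 per arm and a 4-day effect, power would move from about 90% to somewhere between 90% (no gain) and 95%, if the extra R² beyond ABSI group and hospital is 0 to 0.20. It would be about 91% to 94% if the ABSI groups already hold most of the age and burned-area information. At best within the assumed range, the CI half-width falls from 2.40 to 2.15 days.

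Both ranges rest on assumed R² values, on reading the SD of 6 days as a residual SD, and, for the second, on a simple banding model of the index. They leave out the small chance-correlation cost, so at the low end there may be no net benefit. The document cannot settle where in the range the trial lies.

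**What to change.** Before unblinding, pre-specify the primary linear model as treatment, ABSI group and hospital (main effects only), plus age and percentage of total body surface burned as continuous baseline covariates, and sex. Keep ABSI group and hospital, because they are the stratification factors.

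The cost is a sentence in the analysis plan and about three degrees of freedom. All three variables are already recorded at admission, so there is no new data collection and no change to the sample size.

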### Study design

This is a prospective, randomized, double-blind, multi-center clinical trial, conducted in 13 burn care centers in Germany. In total, 150 adult patients with burn and scald injuries will be included.

Via a centralized randomization list, patients are randomly allocated to the drug- or the placebo-treated group. Patients receive normal state-of-the-art burn care treatment plus study medication every other day. Study wound sites (SGDCs and SDWs) are treated with standard wound dressings. Dressing changes, wound documentation, photo documentation, biopsies, control of safety parameters, study medication and other relevant actions are strictly regulated in the study protocol. The acute treatment and observational phase is 28 days, with follow-up controls at Day 42, after 6 months and 12 months after inclusion.

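### The primary healing-time endpoint is fixed as a normal continuous variable, a model that cannot use patients who die, leave or are unhealed when last seen, although up to 36% may lack a healing time

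*Protocol article*

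**What the plan says.** All references are to the Protocol article.

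- Primary endpoint: "The primary endpoint is the time until complete re-epithelialization of the SGDS at a specified location on the lateral upper thigh".
- Statistical analysis: the time taken for "re-epithelialization of the skin graft donor site will be analyzed as a continuous variable with normal distribution". Testing is adjusted for ABSI group and hospital. The analysis population is everyone randomized who received at least one dose.
- Sample size justification: healing under conventional care "occurs after a mean of 10 to 15 days with a standard deviation (SD) of about 6 days". EPO is expected to shorten this by 4 days or more. The resulting requirement is given as follows: "Sample size calculation with alpha = 0.05 and beta = 0.10 thus indicates that 48 evaluable patients per group are necessary". The section seeks 96 patients with valid primary data out of 150 enrolled, calls the analysis of those 96 intention-to-treat, and allows 54 dropouts.
- Study design: "The acute treatment and observational phase is 28 days, with follow-up controls at Day 42, after 6 months and 12 months after inclusion". Under Treatment, the donor site is created on Day 2.
- Secondary endpoints: mortality is counted within 21 days, during the hospital stay and at one year. No expected rate is given.
- Objectives: lower morbidity and mortality under EPO are among the effects sought.
- Discussion: age, burned surface, concomitant illness, infection and other factors are said to strongly affect prognosis, survival and wound healing alike.

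The article prints no rule for a patient who has no healing date.

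**The concern.** A comparison of means under a normal model takes one number per patient. A patient who dies on day 9 with an open donor site, or who leaves on day 12 unhealed, has no such number. What is known about that patient (not healed by day 9 or day 12) cannot enter the model. A time-to-event analysis uses exactly that information.

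This would be a detail if such patients were rare and unrelated to healing. The article suggests neither. It budgets for more than a third of enrolled patients lacking valid data. It counts deaths within 21 days, a span that covers the expected healing time. It names shared causes of poor survival and slow healing, and it hopes that treatment changes mortality. Randomization then no longer protects the comparison of those with a recorded healing day, and the estimated gain in days could move either way.

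The stated population and the stated model also do not fit together. Everyone dosed cannot be analysed under this model unless values are supplied for those without a healing day.

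**Working it through.** **1. The plan's own figure.** Inputs from Sample size justification and Statistical analysis: difference 4 days, SD 6, two-sided alpha 0.05, power 90%, equal groups.

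n per group = 2 × [6 × (1.960 + 1.282) / 4]² = 47.28, rounded up to 48. The printed figure reproduces. At 48 per group, power is 90.4% by the normal formula and 89.8% by the t test. The planning is therefore consistent with the normal model in the analysis section.

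**2. Share without valid data.** 150 − 96 = 54, and 54/150 = 36.0%. The article prints 34%, a separate minor slip. Some of the 54 may never be dosed and would properly leave the stated population. The article does not divide them up, so 36% is an upper figure for dosed patients without a healing day.

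**3. Bias from unequal, informative loss.** The article gives no loss rate by arm and no correlation, so these are assumptions. Take log-normal healing times with mean 12.5 (the middle of 10 to 15) and SD 6, with no true difference between arms. Let a patient lose the endpoint when a latent normal score, correlated rho with log healing time, exceeds the cut-off that gives the stated loss rate. The mean of the observed times is then:

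| rho | 30% lost | 20% lost | 15% lost |
|---|---|---|---|
| 0.5 | 11.01 | 11.41 | 11.62 |
| 0.7 | 10.38 | 10.93 | 11.23 |

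- rho 0.5, 30% against 20%: 11.41 − 11.01 = 0.40 days.
- rho 0.7, 30% against 15%: 11.23 − 10.38 = 0.85 days.

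Against the 4-day target these are 0.40/4 = 10% and 0.85/4 = 21%. If control loses more, its observed mean falls further and EPO looks worse than it is. If EPO loses more, EPO looks better than it is. With equal loss and no true difference, the bias in the difference is zero.

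**4. Outer bound.** With gamma times, if an arm lost exactly its slowest 36%, its observed mean would fall by about 3.6 days (12.5 to 8.90). Losing the slowest 10% moves it by 1.3 to 1.4 days. This is a worst case for a single arm, not a forecast.

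**5. Non-healing alone.** Day 28 is 26 days after donor-site creation and Day 42 is 40 days after. With log-normal times and control means 10 to 15, 2–5% of controls are unhealed at 26 days and about 0.3% at 40 days. Excluding those unhealed at 26 days turns a true 4.0-day effect into 3.7–3.9 days if both arms have SD 6, or 3.3–3.5 days if both have the same coefficient of variation. With a cut at 40 days it stays at 3.9–4.1. Death and withdrawal therefore matter more than slow healing.

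**6. Cost of a time-to-event test.** Simulated log-rank power with 48 per arm, followed to 28 days, is about 78–92% over gamma and log-normal times. The t test on complete data has about 88–91%.

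**The case against.** The strongest reply is that the article condenses a longer protocol. Handling of deaths and missing values commonly sits in the full protocol or the SAP, and neither is shown. That stands as far as it goes. A reader might infer that patients without a healing day are dropped, but no exclusion or imputation rule is printed, so this cannot be stated as fact. The reply does not cover the choice of model, which the article does state, and which has no place for a censored time whatever the handling rule says.

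Three stronger readings are tempting but not supported.

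- *The planning figures contradict normality.* A normal model with SD 6 does put 15.9% of EPO times below zero at mean 6 and 4.8% of control times at mean 10. At means 11 and 15 the shares are only 3.3% and 0.6%. The 48 per group was computed under that same model and reproduces. This shows an approximate model, not a contradiction.
- *The t test wastes power on skewed data.* With complete skewed data it keeps its type I error (3.8–5.3%) and its planned power. A rank test gains (96–99%) for log-normal times with SD 6 in both arms. With equal coefficients of variation both tests reach about 97–99%, and for gamma times the t test is slightly better.
- *Patients unhealed at Day 28 are lost.* A Day 42 control is scheduled, and by then almost nobody is unhealed on the plan's own figures.

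It is also fair to say that the 0.4 to 0.85 days depends wholly on assumed inputs, and that this is a Phase 2a trial.

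**Conclusion.** The concern holds, resting on informative loss of the endpoint. The article fixes a model that cannot use the follow-up of patients who die, withdraw or are unhealed when last seen. It allows up to 36% of enrolled patients without valid data, claims to analyse everyone dosed, and itself gives reasons to expect that loss is tied to slow healing and may differ by arm.

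Under the assumptions in step 3 the bias is about 0.4 to 0.85 days, a tenth to a fifth of the target effect, with a sign that depends on which arm loses more. It would be smaller if loss were balanced or unrelated to healing. That observed healing times alone would be compared remains an inference from the model and from the 96-of-150 budget.

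**What to change.** Before unblinding, reword the primary analysis along these lines:

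- Analyse time from donor-site creation to complete re-epithelialization as a time-to-event endpoint in all dosed randomized patients, adjusted for ABSI group and hospital. State how a dosed patient whose donor site is never created is counted.
- Censor patients not seen to heal at their last wound control, administratively at Day 42. Treat death before healing as a competing event.
- Name one primary test in advance and state its power under the planning assumptions.
- Report a restricted-mean difference in days, so that the result can be read against the 4-day target.
- Keep the normal-theory comparison of observed healing times as a sensitivity analysis.
- Bring the 96-of-150 statement and the definition of the analysis population into line.

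The cost is wording; no new data or patients are needed for the change itself. The effect measure is less simple than a difference in means. A plain log-rank test may have somewhat lower power (about 78–92% at 48 per arm), which is why the power of the chosen test should be stated. The dosed patients without a healing day would add follow-up time to the 96 now counted on.
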